#### Treatment of the common iliac artery

A 6F or 7F sheath (depending on the type and diameter of the stent) is introduced into the ipsilateral common femoral artery. If necessary an adjunctive contralateral approach may be used at the discretion of the physician, either to make angiographic images, or to facilitate passage of the diseased segment. All patients receive 5,000 units of unfractionated heparin. A diagnostic catheter is introduced into the aorta over a 0.035-inch guidewire. Digital Subtraction Angiography (DSA) is performed and saved according to protocol. In stenoses, the pressure gradient is measured using a 70cm straight catheter (4F) without side holes, which is withdrawn through the stenosis. A translesional systolic blood pressure gradient of >10mmHg is considered significant. The pressure gradient, as well as absolute pressures, are documented. The length of the diseased segment is measured per-operatively on the DSA-images, and based on the pressure gradient and length measurement the final decision is made whether or not to include and randomize the subject. Any occlusion is included, as well as any stenosis longer than 3 cm. Serial lesions less than 2 cm apart will be regarded as one long stenosis and will be randomized.

Based on randomisation, an Advanta V12 stent or a balloon-expandable uncovered stent is placed. A stenosis should be fully covered by the stent, including 5mm proximal and distal to the stenosis, based on the inflated length of the stent. In case of proximal lesions, in which the stent would extend into the aorta, and in distal lesions, in which the stent would cover the internal iliac artery (IIA), this 5mm margin is not mandatory. In case of a stenosis including the distal aorta or iliac bifurcation, ‘kissing stents’ will be placed, which will extend into the aorta. In case of a stenosis extending into the EIA, the lesion in the CIA will be treated with a balloon-expandable stent. The stenotic segment extending into the EIA will be treated with PTA alone, PTA and a self-expanding stent or remote endarterectomy. We try to avoid covering the IIA with a stent.

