#### Secondary endpoints

• Reocclusion rate. Defined as complete occlusion of the initially treated target-lesion.

• Target-lesion revascularization (TLR) rate. Defined as the rate and frequency of the need for repeated procedures (endovascular or open surgical) due to a problem arising from the target-lesion (+1 cm proximally and distally to include edge phenomena) in surviving patients with preserved limb.

• Immediate outcome:

– Procedural success. Defined as the combination of technical success, device success and absence of procedural complications.

– Technical success. Defined as successful vascular access and completion of the endovascular procedure and immediate morphological success with less than 30% residual diameter reduction of the treated lesion on completion and a systolic pressure gradient of less than 5 mmHg.

– Device success. Defined as exact deployment of the device, according to the instructions for use, using the assigned device only.

• Clinical outcome:

– Distribution of Rutherford stages during follow-up as compared to baseline.

– Functional outcome:

▪ In patients with IC: Improvement in claudication onset time (COT) and absolute claudicating time (ACT) on standardized treadmill test.

– Improvement in disease-related health status, functioning and quality of life. As defined by the Walking Impairment Questionnaire (WIQ) and RAND-36 questionnaire.

• Hemodynamic outcome:

– Mean and median ABI during follow-up as compared to baseline.

• Morphological outcome:

– Acute diameter gain (change in minimal luminal diameter from base-line to post-intervention.

• Target-extremity revascularization (TER) rate. Defined as the rate and frequency of the need for repeated procedures (endovascular or open surgical) due to a problem arising remote from the target-lesion in surviving patients with preserved limb.

• Mortality rate. Mortality rate associated with the endovascular procedure (that is, mortality within 30 days post-procedure or mortality during a hospitalization >30 days due to the procedure) will be reported separately, as well as overall mortality.

• Complication rate. In contrast with AE’s and SAE’s, which do not need to be related to the treatment, only complications that are (likely) related to the treatment will be reported. This is at the discretion of the investigator.

– Complications will be scored as ‘major’ or minor’. A major complication is a complication that:

▪ Leads to death;

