– Cerebrovascular disease: Known carotid artery disease and history of minor or major stroke or transient ischemic attack (TIA).

• Medication, pre-, peri- and post-procedural, (including dose, frequency and duration of use):

– Anticoagulants (Acenocoumarol, Fenprocoumon, unfractioned or low molecular weight heparins, and so on);

– Antithrombotic agents (Acetyl salicylic acid, Clopidrogel, Dipyridamol, and so on);

– Statins or other lipid-lowering agents;

– Beta-blockers;

– Angiotensin converting enzyme inhibitors;

– Angiotensin-II receptor antagonists;

– Insulin and oral hypoglycaemic agents;

– Medications for the treatment of IC (Pentoxifylline, Buflomedil).

• Baseline anatomic characteristics of the target lesion in the common iliac artery, as determined by DSA and pre-operative CT-angiography or MR-angiography:

– Arterial inflow: Impaired inflow is defined as presence of hemodynamically significant obstruction in the aorta;

– Arterial outflow: Impaired outflow is defined as presence of hemodynamically significant obstruction in the external iliac artery, common femoral artery or both superficial and deep femoral arteries. Isolated hemodynamically significant obstruction in either the superficial or deep femoral artery will not be considered impaired outflow;

Reference vessel diameter, obtained from averaging 5mm segments proximal and distal to the lesion;

Involvement of origin/ostium;

Lesion length, documented in centimeters and classified as follows:

▪ Focal: ≤1 cm;

▪ Short: >1 and <3 cm;

▪ Intermediate: ≥ 3 and < 5 cm;

▪ Long: ≥ 5 cm;

▪ In case of vessel occlusion with a stenosed segment, both the length of the stenosed segment and the length of the occluded segment should be reported.

– Occlusion or stenosis

– In case of stenosis

▪ Minimal luminal diameter;

▪ Percent diameter stenosis;

▪ Systolic pressure gradient, measured as described previously.

– Calcification: Semi-quantitative distinction between no, moderate, and heavy calcification at the site of the lesion.

– TASC-classification.

• Baseline anatomic characteristics of other hemodynamically significant lesions at the aortoiliac and femoropopliteal level:

– Arterial segment(s):

▪ Infra-renal abdominal aorta;

▪ Internal iliac artery;

▪ External iliac artery;

▪ Common femoral artery;

▪ Deep femoral artery;

▪ Superficial femoral artery;

▪ Popliteal artery.

– Lesion length, documented in centimeters and classified as follows:

▪ Focal: ≤1 cm;

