#### Procedure-related parameters

• Grams of intravenous iodine used for contrast. The amount of millilitres used will be scored during the procedure, and post-hoc the amount of iodine will be calculated. In our centre, we use Visipaque®, which contains 320mg of Iodine per ml

• Radiation time and dosage, as is measured by the fluoroscopy device

• Amount and type of materials used (guidewires, sheaths, balloons, catheters)

• Type, diameter, number and length of stents used

• Lesion characteristics after treatment:

– Arterial inflow: Impaired inflow is defined as presence of hemodynamically significant obstruction in the aorta;

– Arterial outflow: Impaired outflow is defined as presence of hemodynamically significant obstruction in the external iliac artery, common femoral artery or both superficial and deep femoral arteries. Isolated hemodynamically significant obstruction in either the superficial or deep femoral artery will not be considered impaired outflow;

– Minimal luminal diameter (MLD);

– Percent diameter stenosis;

– Systolic pressure gradient.

• Peri-procedural complications.

• Technical success

• Device success

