### Randomization, blinding and treatment allocation

All symptomatic patients in whom a hemodynamically significant lesion of the CIA is suspected will be included. This is assessed using DUS and either CT-angiography or MR-angiography. A hemodynamically significant lesion is suspected if DUS shows a peak systolic velocity ratio of ≥2.4 and/or CT-angiography or MR-angiography shows a diameter reduction of ≥50%. Any suspected significant lesion is initially included, and informed consent obtained, even if pre-operative imaging shows a stenosis with a length of less than 3 cm. After the pre-intervention DSA and intra-arterial systolic blood pressure gradient measurement have been performed, the treating physician will make the final decision if the patient meets the inclusion criteria. If there is a stenosis with a length of more than 3 cm, or an occlusion, the patient will be randomized. All patients with stenoses with a length of less than 3 cm will be excluded, but they will be registered, and informed consent will have been obtained to store their data (Figure 2). Randomization will be performed using an online registration and randomization program (Trans European Network for Clinical Trial Services (TENALEA), http://tenalea.net). Unstratified randomization will be used, with a minimization algorithm based on occlusion vs stenosis, and endovascular vs hybrid procedures. If a patient has bilateral iliac lesions that are eligible, the symptomatic limb will be included. In case both limbs are symptomatic, the leg with the lowest ABI will be included. Both legs will receive the same treatment. The patient will be allocated to either the Advanta V12 PTFE-covered stent, or to an uncovered balloon-expandable stent. Patients will be blinded for the treatment they receive. When patients are under local or regional anesthesia, a sterile operating theatre napkin will be placed in such a manner that the patient cannot see the procedure and the stent in particular. The physician will make sure not to mention the type of stent prior, during or after the procedure. The physician performing the procedure will not be blinded, as this is not possible practically. The type of stent used will not be documented in the patient’s medical record. Post-operative ABI’s, DUS and scoring of Rutherford classification will be performed by vascular technicians who are blinded for the type of stent used. Therefore, this is a double-blind study.

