### Statistical analysis

Statistical analysis will be performed for the complete study population, as well as subgroup analysis for patients with IC vs CLI, occlusions vs stenoses, and endovascular vs hybrid procedures.

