## Definitions

ABI, Ankle-brachial index. Defined as the ratio between the highest systolic pressure in both brachial arteries and the highest systolic pressure in the crural arteries. In patients without CLI this is repeated after the standardized treadmill test, termed ‘ABI in rest’ and ‘ABI after exercise’; ABR form, General Assessment and Registration form, is the application required for submission to the accredited Ethics Committee (in Dutch: Algemene Beoordeling en Registratie); Absence of binary restenosis, Absence of hemodynamically significant obstruction (see definition) after endovascular intervention; ACT, Absolute claudication time. Defined as the time (in minutes and seconds) after initiation of the treadmill test when the patient cannot walk any further due to severe the patient cannot walk any further due to severe claudication pain; Aortoiliac level, Proximal limit: Origin of the renal arteries. Distal limit: Deep circumflex iliac artery inguinal ligament; COT, Claudication onset time. Defined as the time (in minutes and seconds) after initiation of the treadmill test when patient first experiences symptoms of claudication; Crural level, Proximal limit: Origin of anterior tibial artery.Including foot arteries; DSA, Digital subtraction angiography. Before and after every intervention a DSA of the aortoiliac level will be performed and saved. DSA will be performed in two imaging planes with at least 30 but preferably more than 45 degrees difference in rotation. DSA will be performed according to a standard protocol; Femoro-popliteal level, Proximal limit: Deep circumflex iliac artery inguinal ligament. Distal limit: Origin of anterior tibial artery; Hemodynamically significant obstruction, Hemodynamic significance can be assessed using the following measurement techniques (in hierarchical order):Intra-arterial translesional systolic blood pressure gradient >10 mmHg as assessed by using a 70cm straight catheter (4F) without side holes which is withdrawn through the stenosis. Intravascular ultrasound (IVUS) measurements indicating ≥50% diameter stenosis. Intra-arterial DSA,indicating ≥50% diameter stenosis. CT-angiography or MR-angiography indicating ≥50% diameter stenosis. DUS indicating ≥50% diameter stenosis as defined by a peak systolic velocity ratio >2.4 (Defined as the ratio of intra-stenotic peak systolic velocity to pre-stenotic peak systolic velocity); MLD, Minimal luminal diameter. The minimal luminal diameter in a stenosis as measured by DSA; Standardized treadmill test, Patients are required to walk with 3.2 km/h at a 12% grade for a maximum of 5 minutes on a treadmill. Claudication onset time (COT) and absolute claudication time (ACT) are determined in minutes and seconds.

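### Acute diameter gain is set for all target lesions, but its baseline value is defined and recorded only for stenoses, so the plan does not fix what an occlusion scores

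*Protocol article*

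**What the plan says.** All places are in the protocol article.

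- **Population.** The secondary objectives include morphological outcome in advanced lesions of the common iliac artery, which the Abstract and the rationale define as stenoses over 3 cm and occlusions. Treatment of the common iliac artery: "Any occlusion is included, as well as any stenosis longer than 3 cm".
- **Endpoint.** Secondary endpoints lists one item under Morphological outcome: "Acute diameter gain (change in minimal luminal diameter from base-line to post-intervention". It carries no restriction by lesion type.
- **Definition.** Definitions gives MLD as "The minimal luminal diameter in a stenosis as measured by DSA".
- **Baseline recording.** Baseline characteristics records "Occlusion or stenosis" for every target lesion. MLD, percent diameter stenosis and pressure gradient then sit under the branch "In case of stenosis".
- **Post-procedure recording.** Procedure-related parameters lists "Minimal luminal diameter (MLD") among the lesion characteristics after treatment, with no such branch.
- **Use of lesion type.** Randomisation is unstratified, "with a minimization algorithm based on occlusion vs stenosis, and endovascular vs hybrid procedures". Statistical analysis plans subgroups that include "occlusions vs stenoses, and endovascular vs hybrid procedures".
- **Analysis.** Comparative statistics says that the secondary endpoints will be compared. Univariate analysis gives an unadjusted t-test or Mann–Whitney test for continuous data and names claudication times and mean ABI, but not acute diameter gain.

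**The concern.** Gain is a difference between two measurements. For an occlusion the article provides the second and, on its wording, not the first. The objective and the endpoint cover both lesion types; the definition and the baseline list cover one.

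Three consequences follow if the text is applied as it stands:

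1. Occlusions have no computable gain, so the endpoint describes only one level of a minimisation factor, and the planned subgroup comparison by lesion type cannot be made for it.
2. Recording can differ between assessors. The article expects occlusions with an adjoining stenosed segment and asks for both lengths. For such a lesion one assessor could leave baseline MLD blank, another could enter 0 mm, and a third could enter the MLD of the adjoining stenosis.
3. An occlusion that cannot be opened has no assigned value. Nothing in the text makes successful passage a condition of randomisation, and patients who receive no treatment stay in the trial under intention-to-treat.

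At stake are the coverage, precision and reproducibility of one secondary endpoint.

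**Working it through.** **The plan's own figures.** The article gives no expected value, SD or sample size for acute diameter gain, so there is nothing to reproduce for this endpoint. The 174 used below as a denominator comes from the primary endpoint. It rests on 79 per group, which reproduces: hazard ratio ln(0.90)/ln(0.72) = 0.321; Freedman, two-sided 0.05, 80% power gives 30 events; 30/0.19 = 157.9 patients, or 79 per group. The article then enrols 87 per group to allow for loss to follow-up. Nothing here changes that number.

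**Side by side.**

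| Lesion | Baseline MLD listed | Post-procedure MLD listed | Gain as written |
|---|---|---|---|
| Stenosis | yes | yes | computable |
| Occlusion | no | yes | not computable |

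**Inputs that the article does not give (all assumed).** Occlusion share q = 0.3, 0.5 or 0.7; final lumen 8 mm in both lesion types (within the 5 to 10 mm diameters of the covered stent); mean baseline MLD in stenoses m = 2 or 3 mm; baseline lumen 0 mm in occlusions.

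**Formulas.**
- Stenoses only: mean gain = 8 − m.
- All lesions: mean gain = q × 8 + (1 − q) × (8 − m).
- Difference, all minus stenoses only = q × m.
- Patients left = 174 × (1 − q).

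| q | Patients left | m = 2: stenoses / all (mm) | Shortfall | m = 3: stenoses / all (mm) | Shortfall |
|---|---|---|---|---|---|
| 0.3 | 122 | 6.0 / 6.6 | 0.6/6.6 = 9% | 5.0 / 5.9 | 0.9/5.9 = 15% |
| 0.5 | 87 | 6.0 / 7.0 | 1.0/7.0 = 14% | 5.0 / 6.5 | 1.5/6.5 = 23% |
| 0.7 | 52 | 6.0 / 7.4 | 1.4/7.4 = 19% | 5.0 / 7.1 | 2.1/7.1 = 30% |

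**Sensitivity to the assumed lumens.** Take instead a reference diameter of 8 mm, post-procedure MLD of 7.2 mm, baseline stenosis of 50% to 90% (m = 4.0 to 0.8 mm) and shares of 20% to 60%. The shortfall then runs from 0.2 × 0.8 / 6.56 = 2% to 0.6 × 4.0 / 5.6 = 43%, with 139 down to 70 patients left.

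**Sensitivity to failed recanalisation.** Let a fraction f of occlusions stay closed, with final lumen 0 mm. The mean gain in occlusions is 8 × (1 − f), and the difference, all minus stenoses only, becomes q × (m − 8f). It is zero at f = m/8, which is 25% for m = 2 and 37.5% for m = 3. Above that, the stenosis-only mean is the higher one.

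**Precision.** If the SD within lesion type is similar, leaving out a share q widens the confidence interval by 1/√(1 − q): 1.20 at 0.3, 1.41 at 0.5 and 1.83 at 0.7. Unopened occlusions scored 0 mm would add spread, so the gain from keeping occlusions may be smaller than this.

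**The case against.** The strongest reply is that the stenosis branch is an ordinary form skip. MLD is measured where there is a lumen to measure; an occluded artery has a lumen of 0 mm; and lesion type is recorded for everyone, so gain in occlusions can be derived from data already collected. Read strictly, the definition would also leave MLD undefined after treatment in any stented artery without residual stenosis, which the post-procedure list shows is not intended. Coding an occlusion as 0 mm could sit in a case report form or analysis plan that is not shown, and the article ties its definitions to an outside consensus.

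Much of this stands. A reader might infer that every occlusion drops out. The article states no such exclusion; that is only what the wording produces if followed to the letter. The remedy indeed needs no new data.

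It does not dispose of the point. The article does more than stay silent on a coding detail: it states an endpoint, a definition and a recording list that do not fit together for an eligible lesion type. That a value of 0 mm could be derived does not mean that it will be, and the mixed lesion and the unopened occlusion remain open to different entries.

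A reader might also infer that occlusions lose all morphological assessment. They do not: technical success includes residual diameter reduction below 30%, applies to occlusions, and is among the outcomes to be tested. Acute gain is the only item under the Morphological outcome heading, not the only morphological measure.

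**Conclusion.** The point holds as a minor definitional gap in one secondary endpoint. Acute diameter gain is set for all advanced lesions, while its baseline component is defined and listed only for stenoses. If occlusions are left out as a result, the endpoint describes stenoses only and loses precision in proportion to their share.

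The size cannot be fixed from the article, because it gives neither the occlusion share nor the lumens. The 9% to 30% shortfall, and the wider 2% to 43%, rest on assumed inputs and on similar final lumens in both lesion types.

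Two stronger conclusions are not supported. One is that the reported mean gain will be too low: that requires both the exclusion and enough opened occlusions, and a stenosis-only mean is in any case a correct figure for stenoses. The other is that the comparison of covered with uncovered stents is biased: lesion type is a baseline feature and a minimisation factor, so leaving occlusions out should affect both arms alike. The primary endpoint and the 174 patients are unaffected.

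**What to change.** 1. In the baseline target-lesion list and in the MLD definition, state that an occluded target lesion has a baseline MLD of 0 mm and a percent diameter stenosis of 100%, also where a stenosed segment adjoins the occlusion.
2. State that post-procedure MLD is 0 mm for an occlusion that was not opened.
3. Compare acute diameter gain in all randomised limbs with adjustment for occlusion versus stenosis, for example by a linear model with arm and lesion type, in place of the unadjusted test. Lesion type is already a minimisation factor and is closely tied to gain, because for an occlusion gain equals the final lumen. Show the results by lesion type as well.

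The cost is two definition lines, a default in the case report form and slightly more analysis work. No new measurement and no change in sample size are needed. If the sponsor means the endpoint for stenoses only, saying so would also remove the contradiction, but it would give up the coverage and precision described above.

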**Figure 2 F2:**
[figure not shown]
Flowchart describing the inclusion and randomization of patients.

In both centers, we have, as a standard procedure, a separate file in which the product sticker of every placed stent is put, coupled with the name, birth date and patient number of the patient that received the stent. Neither the patient, nor the personnel who perform post-operative investigations, nor the analyst analyzing the data have insight in to this file; therefore keeping this file does not threaten the double-blind nature of this study.

The indication for breaking the randomization code is the need for open surgical or endovascular re-intervention if the treating physician feels this is required. The physician will then contact the coordinating or one of the principal investigators, who will reveal the type of stent and document breaking of the randomization code. Alternatively, this can be looked up in the separate file described in the previous paragraph.

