#### Adverse and serious adverse events

Adverse events are defined as any undesirable experience occurring to a subject during the clinical trial, whether or not considered related to the investigational treatment. All adverse events reported spontaneously by the subject or observed by the investigator or his staff will be recorded.

A serious adverse event is any untoward medical occurrence or effect that:

• Causes death, or is life threatening (at the time of the event);

• Requires hospitalization or prolongation of existing inpatients’ hospitalization;

• Results in persistent or significant disability or incapacity.

All SAEs will be reported by the responsible investigator through the web portal ToetsingOnline to the accredited METC that approved the protocol within 15 days after the sponsor has first knowledge of the serious adverse reactions.

SAEs that result in death or are life threatening should be reported expeditiously. The expedited reporting will occur not later than 7 days after the responsible investigator has first knowledge of the adverse reaction. This is for a preliminary report, with another 8 days for completion of the report.

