#### Data safety monitoring board

Following the recommendations of the ’Quality assurance in human medical research’ charter (Dutch: Kwaliteitsboring van mensgebonden onderzoek) by the ‘Dutch Federation of Academic Medical Centers’ (Dutch: Nederlandse Federatie van Universitair Medische Centra), we do not consider the formation of a Data Safety Monitoring Board (DSMB) sensible. A DSMB has several functions. First, is to assess whether statistical significance can still likely be reached or, on the other hand, may be reached preliminarily for the main outcomes, and thus whether the study group size should be changed. However, our main outcomes are all scored at 2 years. So, when a relevant group has reached the 2-year follow-up, and an interim analysis would be sensible, we will already have included all of our patients. So, the interim analysis would not contribute anything on that field.

A second function of the DSMB is to assess the safety and (S)AE’s of the investigational products. However, all stents that are used in the trial are registered for use in the iliac artery and have been used for years. As well, virtually all complications are procedure-related and not stent-related. Therefore, a difference in safety or occurrence of (S)AE’s is unlikely. Of course, the investigators and the METC will monitor the occurrence and rate of (S)AE’s.

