#### Univariate analysis

Univariate analysis will be performed to assess differences in the other aforementioned primary and secondary endpoints.

Continuous data: Averages with standard deviation (parametric data) or medians with percentiles (non-parametric data) will be calculated. Differences between both groups will be tested using a Student’s *t*-test (parametric data) or a Mann–Whitney *U*-test (non-parametric data). Differences with a *P*-value <0.05 will be considered statistically significant. The following endpoints will be assessed:

Post-intervention COT and ACT;

Mean ABI.

Categorical data: Frequencies will be calculated and difference between both groups will be tested using Chi-squared test. Differences with a *P*-value <0.05 will be considered statistically significant. The following secondary endpoints will be assessed:

• Target lesion revascularization rate and target extremity revascularization rate;

• Procedural, technical and device success rate;

Mortality rate, complication rate, amputation rate;

• Rate of device-specific problems.

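### The complication-rate comparison counts only events the investigator judges treatment-related, and no blinded person is assigned to that judgement

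*Protocol article*

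**What the plan says.** The Secondary endpoints section separates the complication rate from adverse and serious adverse events, which need not be related to treatment. For complications, "only complications that are (likely) related to the treatment will be reported. This is at the discretion of the investigator". Events that count are graded major or minor and placed in four categories: access site, treatment site, organ-specific and systemic. Procedural success is defined there partly by the absence of procedural complications.

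Under Univariate analysis, the endpoints tested between arms include "Mortality rate, complication rate, amputation rate". The method is: "Frequencies will be calculated and difference between both groups will be tested using Chi-squared test". Procedural success is in the same list. Adverse and serious adverse events are not.

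On blinding, the section on randomization says: "The physician performing the procedure will not be blinded, as this is not possible practically". Blinded staff are named for particular measurements: "Post-operative ABI’s, DUS and scoring of Rutherford classification will be performed by vascular technicians who are blinded for the type of stent used". The Standardized treadmill test section adds treadmill testing. On the file linking patients to stents: "Neither the patient, nor the personnel who perform post-operative investigations, nor the analyst analyzing the data have insight in to this file". Investigators are not among those excluded, and the coordinating and principal investigators can reveal the stent type when the code is broken.

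The section on adverse and serious adverse events states: "All adverse events reported spontaneously by the subject or observed by the investigator or his staff will be recorded".

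**The concern.** A relatedness judgement decides which events enter a between-arm test. If the person judging knows the stent, the same event can be called related in one arm and unrelated in the other. The test then compares attribution habits as well as event rates. This can produce a difference where none exists or shrink a real one. Events recorded without regard to relatedness would avoid the problem, and the protocol collects them, but the comparison it lists uses the filtered version. There is no data safety monitoring board and no planned interim analysis. The trial's published complication comparison is therefore where an imbalance of this kind would be seen or missed.

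**Working it through.** **1. Who makes the judgement, and can that person know the stent?**

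| Assessment | Who does it | Blinded? |
|---|---|---|
| ABI, duplex, Rutherford, treadmill | Vascular laboratory staff | Yes, stated |
| Analysis of the data | Analyst | No access to the stent file, stated |
| Complications during the procedure | Not named; documented during the operation | Operator knows the stent, stated |
| Complications in the first 30 days | Not named | Not stated |
| Relatedness of a complication | The investigator, at discretion | Not stated |

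The protocol assigns blinding assessment by assessment, and the relatedness judgement receives none. That it may be made by someone who knows the stent is an inference from the operator's position and the lead investigators' access. It is not stated.

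**2. Which comparisons pass through the filter?** The complication rate does, by definition. Procedural success may, because it requires absence of procedural complications and the text does not say whether the filter applies there. Overall mortality, amputation, target-lesion revascularization and device-specific problems do not. Nor does the primary endpoint, absence of binary restenosis.

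**3. What could it do to the test?** The protocol gives no expected complication rate, so there is no complication figure to reproduce. The only input taken from it is 87 patients per arm. The 79 behind that number reproduces. HR = ln 0.90 / ln 0.72 = 0.321. Events = (1.960 + 0.842)² × [(1 + 0.321)/(1 − 0.321)]² = 29.67. Then 29.67 / (0.10 + 0.28) = 78.08, rounded up to 79, and 79 × 1.10 = 86.9, or 87.

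The rest is assumption. Let the true event rate r be the same in both arms and let fractions a₁ and a₂ of events be judged related. Counted events are binomial with n = 87 and probabilities r·a₁ and r·a₂. The pooled two-proportion z test, equivalent to the chi-squared test without continuity correction, rejects when |x₁ − x₂|/87 exceeds 1.96 × √[2p̄(1 − p̄)/87], with p̄ = (x₁ + x₂)/174. Summing the exact binomial probabilities over the rejection region gives:

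| True rate, both arms | 70% v 70% | 80% v 90% | 70% v 90% | 60% v 90% |
|---|---|---|---|---|
| 5% | 4.4% | 4.5% | 5.4% | 6.9% |
| 15% | 5.0% | 5.9% | 9.2% | 15.4% |
| 20% | 4.9% | 6.2% | 10.7% | 19.3% |
| 25% | 4.8% | 6.9% | 12.9% | 24.1% |

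Check by normal approximation at r = 20% and 60% v 90%. The counted rates are 0.12 and 0.18 (10.4 v 15.7 expected events out of 17.4 true events per arm). The null standard error is √(2 × 0.15 × 0.85 / 87) = 0.0541. The alternative standard error is √[(0.12 × 0.88 + 0.18 × 0.82)/87] = 0.0539. The upper tail starts at (1.96 × 0.0541 − 0.06)/0.0539 = 0.85, giving about 19.6%. With the other tail the total is 19.7%, close to the exact 19.3%.

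**4. The opposite case.** With assumed true rates of 15% v 30%, the same test has 67% power on all events and 54% if 80% are counted in both arms. Power is 25% if 90% are counted in the better arm and 70% in the worse. Even an even-handed filter costs power.

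**The case against.** The strongest reply is that a reader might infer more than the text supports, in four ways.

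- **That the judging investigator is stated to be unblinded.** Only the operator is. Stent type is kept out of the medical record, and a follow-up physician who did not operate would ordinarily learn it only through a documented code break or the separate file. This stands: the exposure is plausible, not established for every judgement.
- **That the whole safety result depends on opinion.** It does not. Mortality, amputation, target-lesion revascularization and device-specific problems are compared without the filter, and device-specific problems lie closest to device safety.
- **That the investigators' prior belief biases the filter.** The section on the data safety monitoring board holds that complications come from the procedure, not the stent: "Therefore, a difference in safety or occurrence of (S)AE" is then described as unlikely. But the filter asks about relation to the treatment, so procedure-related events pass it. The belief gives no reason to drop events and favours neither arm.
- **That the protocol omits safety tables by arm.** A protocol article commonly leaves these to the full protocol or analysis plan, so their absence is not counted as an error.

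Discretion is also narrower than the endpoint wording suggests. Access-site and treatment-site events leave little room for dispute, and the follow-up sections have any complication during the procedure documented and any in the first 30 days scored. An attribution gap across all events is therefore severe. If half of the events were always counted and the other half were attributed 60% v 80%, the overall gap would be 80% v 90% (0.5 × 100% + 0.5 × 60% = 80%; 0.5 × 100% + 0.5 × 80% = 90%), the mild column of the table.

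What remains is that a stated rule makes entry to a between-arm test discretionary, without assigning the judgement to anyone blinded.

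**Conclusion.** The point holds for the complication rate and possibly for procedural success. It is a secondary-endpoint matter and a cheap improvement rather than a threat to the trial's main conclusion. Direction and size cannot be derived from the documents. On assumed event rates of 15% to 25%, the rejection rate of a nominal 5% test runs from about 6% to 7% at a 10-point attribution gap (80% v 90%) to 15% to 24% at a 30-point gap (60% v 90%). At a 5% event rate the effect is negligible to small, about 4.5% to 7%. These figures assume equal true rates, 87 analysed patients per arm and a gap that applies to all events. They illustrate what the rule permits and do not estimate what will happen.

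**What to change.** In Secondary endpoints and in Univariate analysis, add a comparison by randomised arm of all serious adverse events regardless of relatedness, within 30 days and over 2 years. Keep the investigator-attributed complication rate as a supportive endpoint.

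The protocol already records these events, so the cost is one table. Background events unrelated to either stent will add some noise. The comparison also does not cover non-serious complications, for which the filtered rate remains the only listed comparison. Extending it to all events meeting the criteria for a major complication would cost more, because the protocol defines that grading for complications only, so unrelated adverse events would need extra scoring.
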